### Mediation analyses

If the data have low levels of missingness, we will also conduct a mediation analysis to assess the hypothesis that the treatment effect on maternal sensitivity is partially mediated by maternal mental health. This analysis will use the propensity scores, as already described, and test the effect of this on maternal sensitivity via the maternal mental health outcomes *after* treatment.

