### Objectives

The current study will examine the causal effectiveness of the Baby Steps intervention in a real-world setting, within a socioeconomically deprived and ethnically diverse area in Bradford. Baby Steps is commissioned by Better Start Bradford and delivered by Action for Children. The authors of this study are independent of the delivery or design of the service.

This study will use a matched-control comparison group. The specific aims of this study are to (1) assess whether the universally and remotely delivered Baby Steps programme is effective in improving the primary outcome of postnatal maternal sensitivity and (2) the secondary outcome of postnatal maternal mental health when compared to services as usual at 6–10 weeks postnatal. This study also aims to (3) assess whether the effects of Baby Steps on postnatal maternal sensitivity are mediated by postnatal maternal mental health.

This study has additional objectives with outcomes nested in routinely linked data, however, it will be underpowered to ascertain causal effectiveness in these outcomes. We aim to (4) assess differences in birth outcomes (delivery type, weight, gestation, feeding) and (5) assess differences in the identification and prevalence of poor perinatal mental ill health inferred through routine data linkage across the two groups. Finally, the economic analysis of this study will (6) estimate the cost of the intervention (including delivery and training to deliver Baby Steps) and (7) assess the feasibility of collecting health related resource use data for a future full economic evaluation.

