### Data collection procedures

The study will include all women recruited from 1^st^ May 2022, up until the end of the delivery of the service (anticipated to be at the end of 2023).

Pregnant women complete a detailed questionnaire when recruited to BiBBS regarding their prenatal attachment, mental health, socio-demographics, family circumstances and more. Data provided from this questionnaire will enable intervention and control groups to be matched, where individual intervention participants can be matched to > 1 control group participant(s) (see statistical methods section for details).

All BiBBS mothers will complete outcome measures at 6–10 weeks after birth. The data are collected either by phone or at a physical home visit. The questionnaires include: the Patient Health Questionnaire-8 (PHQ-8), Generalised Anxiety Disorder assessment-7 (GAD-7), and the Mothers Object Relations Scale-Short Form (MORS-SF) (see below for details).

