#### Propensity score matching

A matched control group to the intervention group will be created using the propensity score matching method. The propensity score is the probability of a subject to receive a treatment conditional on the set of covariates [7]. The propensity score method with ‘one-to*-many’* matching will be applied to maximise statistical power [3], as we can utilise data from the BiBBS cohort for mothers who do not participate in Baby Steps.

Figure 1 presents a simplified Directed Acyclic Graph (DAG) created to identify confounding variables that are associated with both the treatment and the outcome [45, 52]. Figure 1 indicates the seven characteristics that we will match the groups on to estimate the effect of treatment on outcome.

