**Fig. 1 Fig1:**
[figure not shown]
Directed Acyclic Graph of associations between confounders, treatment exposure, and primary outcome

Table 2 describes the covariates that we will use for propensity score matching obtained from the BiBBS baseline questionnaire completed before the child is born. All matching variables are at the level of the mother, not the child. Variables were selected to be matched upon if they were thought to have an association with both uptake of treatment, and with the outcomes (maternal sensitivity, maternal mental health), and there was empirical evidence to suggest this was the case (see references in Table 2).

**Table 2 Tab2:** Covariates for matching obtained from BiBBS baseline questionnaire

Covariates (measurement tool if relevant)	Measurement	Justification
Prenatal attachment (Prenatal Attachment Inventory)	Continuous	[13]
Prenatal Depression (PHQ-8)	Continuous	[13]
Prenatal Anxiety (GAD-7)	Continuous	[13]
Ethnicity	Categorical	[13, 41, 51]
Socioeconomic position (financial security)	Continuous	[28, 48, 51]
Mother age	Continuous	[13, 28]
Parity (first child or not)	Continuous	[48]
Speaks English	Binary	[11, 51]

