### Linear regression analyses 

After matched groups have been created, linear regression analyses will be run using group assignment as the independent variable, and the primary (maternal sensitivity) and secondary outcomes (maternal mental health) as the dependent variables. In addition to group assignment, two covariates will be included in the model: child age in days will be included as a continuous covariate, and Better Start Bradford area will be included as a categorical covariate with 3 levels. Models will be run for each outcome: maternal child sensitivity (MORS-SF), maternal depression (PHQ-8), and maternal anxiety (GAD-7).

We will conduct both Intention to Treat (ITT) analyses to ascertain the effects of enrolling in the intervention [23, 27], and per protocol analyses to ascertain the effects of receiving the treatment [50]. The ITT analyses will therefore include all mothers who enrolled in the intervention after an initial home visit, and the per protocol analyses will only include ‘completers’, defined as those who take part in at least 6 sessions (including at least one postnatal session).

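### The mediation analysis for aim 3 rests on propensity scores, which do not remove confounding between postnatal mental health and maternal sensitivity, so it can show a false indirect effect if Baby Steps changes mental health

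*Protocol article*

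**What the plan says.** The Objectives section lists as aim 3 to "assess whether the effects of Baby Steps on postnatal maternal sensitivity are mediated by postnatal maternal mental health". The Mediation analyses section gives the method: "This analysis will use the propensity scores, as already described", and the analysis will "test the effect of this on maternal sensitivity via the maternal mental health outcomes" measured after treatment.

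The score itself is defined under Propensity score matching: "The propensity score is the probability of a subject to receive a treatment conditional on the set of covariates". Its covariates (Table 2) were chosen for "an association with both uptake of treatment, and with the outcomes (maternal sensitivity, maternal mental health"). They include prenatal attachment, prenatal PHQ-8 and prenatal GAD-7. The figure caption describes a "Directed Acyclic Graph of associations between confounders, treatment exposure, and primary outcome" and names no mediator. The graph itself was not available to me, so I put little weight on that.

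For the regressions after matching, Linear regression analyses states that besides group "two covariates will be included in the model": child age and Better Start Bradford area.

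On timing, Data collection procedures says "All BiBBS mothers will complete outcome measures at 6–10 weeks after birth". PHQ-8, GAD-7 and MORS-SF are all in that set.

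**The concern.** A mediation claim needs two kinds of confounding control: between treatment and the other variables, and between mediator and outcome. A propensity score for treatment addresses the first. It does not address the second, because women with high and low postnatal PHQ-8 within the same group still differ in prenatal depression, anxiety and attachment.

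The protocol's own text makes such confounding likely. It selected the Table 2 covariates because they were thought to relate to both maternal sensitivity and maternal mental health, and it notes that MORS-SF is associated with maternal depression. If these prenatal factors are left out of the models, their effect on MORS-SF is partly credited to postnatal mood.

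At stake is the answer to one of the three specific aims. A positive result would be read as evidence that Baby Steps works on sensitivity through mental health. The Objectives section cautions that the routine-data outcomes cannot support causal conclusions, but gives aim 3 no such caution.

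**Working it through.** **Planning figures reproduced.** The protocol gives no figure for the mediation analysis. Its related figures hold. With a two-sided 5% t-test, d = 0.50 at 65:65 has 80.8% power. With d = 0.42, power is 82.1% at 95:95 and 81.5% at 62:187. All meet the stated 80%.

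**Inputs from the protocol.** Effect on the mediator a = 0.42 SD (the planning difference for PHQ-8 and GAD-7); MORS-SF SD 4.7; target difference 2.35; group sizes 65:65 and 62:187.

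**Assumptions.** No true mediator-to-outcome path. A prenatal score, balanced between groups, correlates r_m with the mediator and r_y with MORS-SF within groups. The documents give neither correlation, so I use a range. Signs are dropped; only size matters here.

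**Size of the bias.** If the outcome model holds group and mediator but not the prenatal score, the mediator coefficient is r_m × r_y instead of 0. The spurious indirect effect is a × r_m × r_y.

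- r_m = 0.3, r_y = 0.2: 0.42 × 0.06 = 0.025 SD; × 4.7 = 0.12 points.
- r_m = 0.6, r_y = 0.4: 0.42 × 0.24 = 0.101 SD; × 4.7 = 0.47 points; 0.47 / 2.35 = 20% of the target difference.

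**How often mediation is falsely declared** (both paths significant at 5%; 4,000 simulated samples per row):

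| Groups | r_m / r_y | Treatment-to-mediator path significant | Mediator-to-outcome path significant | Both | Both, prenatal score in both models |
|---|---|---|---|---|---|
| 65:65 | 0.3 / 0.2 | 66% | 11% | 7% | 3% |
| 65:65 | 0.5 / 0.3 | 66% | 41% | 26% | 4% |
| 65:65 | 0.6 / 0.4 | 66% | 79% | 51% | 5% |
| 62:187 | 0.3 / 0.2 | 82% | 15% | 12% | 4% |
| 62:187 | 0.5 / 0.3 | 82% | 65% | 53% | 4% |
| 62:187 | 0.6 / 0.4 | 82% | 97% | 79% | 4% |

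A separate run of the two end scenarios gave 8% and 54% at 65:65, and 13% and 78% at 62:187. The two runs differ by at most three percentage points. With direct adjustment the mean indirect effect is about 0.

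**Score also used as a covariate.** A second simulation used nearest-neighbour matching on two covariates and also entered the score in the models. One covariate had strength k on both mediator and outcome (k = 0.3, 0.5, 0.7, assumed). Mediation was falsely declared in 5.7%, 27% and 74% of samples at 65:65, and 9.8%, 55% and 92% at 62:186. The mean spurious effect was 0.02, 0.06 and 0.14 SD. Entering the covariates individually gave 2 to 6%. A single score that blends several covariates does not stand in for the one that drives mood and MORS-SF.

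**No effect on mental health.** With a = 0, the same simulation gave a mean indirect effect near 0 and at most about 6% false declarations.

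**Cause not measured at baseline.** If the shared cause is unmeasured, or arises at the common postnatal contact, the rates at k = 0.3, 0.5 and 0.7 are 11%, 54% and 66% at 65:65, and 23%, 80% and 81% at 62:187. Adjusting for baseline covariates does not remove this part.

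**The case against.** The strongest reply is that the mediation section is very short, that a detailed analysis plan is to be preregistered, and that the text says propensity scores will be used, not that nothing else will be. The covariates needed are already collected, and nothing rules out adding them. That is fair, and the unseen plan may do so. But the article does more than omit a detail. It names a method of confounding control for this analysis, and that method does not address the mediator–outcome part. The timing of the measures is also fixed by the design.

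A second reply is that with a single prenatal score, entering the propensity score as a covariate would remove the bias, since each is a function of the other. That is true for one covariate. Table 2 has several, and the second simulation shows bias remaining.

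Third, aim 3 is conditional and is not mentioned in the abstract, so it is a lesser aim. That limits the weight of the point.

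Some stronger readings are not supported:

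- A reader might infer that the propensity score itself is the exposure. The sentence before states the hypothesis as a mediated treatment effect, and the regression section makes group assignment the independent variable.
- A reader might fault running the analysis only if missingness is low, given that imputation is planned. This is a cautious choice and contradicts nothing.
- A reader might take the 97% in the table as the rate of false mediation. It is the mediator-to-outcome path alone, in the strongest scenario.

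**Conclusion.** The point holds as a weakness in the stated method for aim 3. Propensity matching leaves prenatal mental health and attachment unbalanced across levels of postnatal PHQ-8 and GAD-7, and this can create an indirect effect where there is none. Over the assumed correlations the bias is about 0.03 to 0.10 SD, or 0.1 to 0.5 MORS-SF points. The chance of falsely declaring mediation is about 8 to 54% at 65:65 and 13 to 78% at 62:187.

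The result depends on two conditions: prenatal correlations that the documents do not give, and a non-zero group difference in postnatal mental health. It would be too strong to say that mediation will be reported whenever Baby Steps changes mental health; at the weak end the excess over 5% is small.

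Measuring mediator and outcome by self-report at one contact is a separate limit. The direction between them cannot be established, and no adjustment repairs that. The primary and secondary treatment-effect estimates are not affected.

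**What to change.** In the statistical analysis plan:

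1. Enter prenatal PHQ-8, GAD-7, prenatal attachment and the other Table 2 covariates directly in both the mediator model and the outcome model, in addition to the matching.
2. Add a sensitivity analysis showing how strong residual mediator–outcome confounding would have to be to explain the indirect effect.
3. Report aim 3 as exploratory, and give the shared 6–10 week self-report as the reason.

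No new data are needed. The cost is a little more analysis work, a few degrees of freedom, and a softer conclusion for aim 3.

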### Economic analysis

The economic analysis will:Assess the feasibility of collecting health related resource use data through routine data and whether the quality of these data allow comparison of groupsAssess the feasibility of collecting a range of consequences that could be used in a cost-consequence analysisAssess the feasibility of linking short term health outcomes measured in the datasets, to longer term costs and outcomes that are more appropriate for a full economic evaluation

Where routinely linked data allow, we will provide descriptive estimates of resource use and outcomes in each group. We will estimate the cost of the intervention and who that cost falls upon. We will explore the potential to extend the time horizon of the analysis by using an existing model to link short term study outcomes to lifetime as the benefits (and potentially costs) of the intervention are likely to impact far beyond the period assessed in the study.

#### Descriptive data

As birth outcomes and the proxy poor perinatal mental health outcomes are categorical, the required sample sizes for detecting differences in these outcomes is very large and unlikely to be obtained within this evaluation. We therefore do not expect to be able to assess effectiveness in these outcomes, but will report descriptive trends in birth outcomes, and in poor perinatal mental health for the intervention and control groups in our analysis.

#### Missing data methods

The most efficient method of handling missing data in propensity score matching depends on the mechanism of missing data in the matching variables, and whether there is unmeasured confounding. The missing indicator method and/or multiple imputation may be used depending on these factors for handling missing data in the matching variables [14]. If missing data are higher than 5% in any of the other variables (child age, maternal mental health and maternal sensitivity), then multiple imputation will be used to handle missing data [43]. If items are missing within any measurement tools, then missing data rules from the measure developer will be followed where available (e.g. within the PHQ-8). We will conduct a secondary analysis including only participants with complete data, and compare this to the primary analysis where missing data is handled. More detail will be provided on handling missing data in a statistical analysis plan.

### Sample size calculations

Sample size calculations for our primary and secondary outcomes were produced using Stata-17’s *power* command for the effectiveness outcomes. Sample size calculations were based on two sample means t-test with a two-tailed alpha of 5%.

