### Intervention

Baby Steps is a ‘relationship-based’ antenatal parent education programme developed by the NSPCC (https://learning.nspcc.org.uk/services-children-families/baby-steps).

Baby Steps delivery begins around the 26th to the 30th week of pregnancy. The programme under evaluation differs to the original programme in that it is delivered to groups remotely but retains some face-to-face contact. To adapt to remote delivery, the service delivery team have condensed the intended nine individual sessions into six group sessions. There are two one-to-one initial sessions (one of which is in the participant's home, one of which is virtual) prior to the course commencing to help build relationships between families and practitioners. Then there are four online, remote, group sessions before the baby is born. After the baby is born there is another in person home visit, followed by two online group sessions. See Table 1 for an overview of the sessions and timings.

**Table 1 Tab1:** Overview of programme content and timings

Content	Time of delivery

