##### Process outcomes

The process evaluation will aim to include both mothers and co-parents. The service collects information on which sessions parents attend and the number of sessions they attend, and group level information about the number of sessions delivered per programme and the deliverer for each session. Parent satisfaction questionnaires are also collected at the end of the programme. This information will be used to further explore effectiveness findings.

A process evaluation will explore parent’s experience of the course, identify the outcomes they reported after attending, and identify the barriers and facilitators to engagement of parents. The plans for this study will be specified in a separate protocol.

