#### Maternal-child sensitivity (MORS-SF)

In the absence of a minimum clinically important difference for the MORS-SF, we based our sample size calculations on 0.5 of a standard deviation in the MORS-SF [16]. A recent study of a trial delivered in Better Start Bradford indicates that the standard deviation in the MORS-SF is 4.7 [9]. We will have 80% power to detect 0.5 of this difference in the MORS-SF (± 2.35, *d* = 0.50) with 130 participants total (65:65), or if we obtain a larger control group through the BiBBS additional sweep (e.g. 140 total (56:84), 150 total (50:100), 180 total (45:135)). Historical data from Baby Steps in Bradford indicate that there is approximately a 40% attrition rate between enrolling and completing the project. To detect a difference in the MORS-SF, Baby Steps should therefore aim to enrol at least 72 participants to achieve the minimum sample size of 45 participants in the intervention group at the end of the study.

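### Intervention women attend Baby Steps in groups, but the sample size and the stated regression treat all women as independent, so the 80% power figures hold only if within-group correlation is close to zero

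*Protocol article*

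**What the plan says.** All places are in the protocol article.

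- **Intervention and Table 1.** After two one-to-one contacts, "Then there are four online, remote, group sessions before the baby is born". A home visit and two further online group sessions follow the birth. That makes six group contacts and three one-to-one contacts. Each session is led by an early years practitioner and a health practitioner.
- **Eligibility.** Comparison women must never have received Baby Steps, so they belong to no course group.
- **Sample size calculations.** "Sample size calculations were based on two sample means t-test with a two-tailed alpha of 5" per cent. For the MORS-SF, "we based our sample size calculations on 0.5 of a standard deviation in the MORS-SF", and "the standard deviation in the MORS-SF is 4.7". The section on maternal-child sensitivity then says "We will have 80% power to detect 0.5 of this difference in the MORS-SF" "with 130 participants total (65:65"), or with unequal splits down to 45:135. For PHQ-8 and GAD-7 the splits run from 95:95 to 62:187 at d = 0.42. The service has been advised to enrol 99 women on that basis.
- **Linear regression analyses.** "linear regression analyses will be run using group assignment as the independent variable", with child age in days and three-level area as the only covariates.
- **Process outcomes.** The service records attendance and "group level information about the number of sessions delivered per programme and the deliverer for each session".

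No group size, number of groups, ICC, design effect, course-group term or cluster-robust variance appears in the article.

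**The concern.** This is a partially nested design: women in one arm are grouped and women in the other are not. Women on the same course share sessions and peers, and may share facilitators. The programme is built on relationships, and the outcomes are maternal sensitivity, depression and anxiety, so some positive correlation within a course group is plausible.

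A two-sample t-test sizing assumes that this correlation is zero. The three-level area covariate does not replace a course-group term, because it does not identify which women sat in the same course.

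Two things are at stake. Power would be lower than stated, for a sample size that already looks settled. And if the analysis also ignores the grouping, confidence intervals would be too narrow and the real type I error would exceed 5%, for the primary and both main secondary outcomes.

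**Working it through.** **Inputs from the article.** Two-sided alpha 0.05. MORS-SF: SD 4.7 and difference 2.35, so d = 0.50. PHQ-8 and GAD-7: d = 0.42. Splits 65:65 and 45:135 (MORS-SF), 95:95 and 62:187 (PHQ-8 and GAD-7).

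**Assumed, because not given.** Analysed women per course group, m = 4 to 10. ICC = 0.01 to 0.10.

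**Step 1: reproduce the stated figures under independence.** The exact noncentral t gives 80.8% power at 65:65 (64 per arm, 128 in total, already suffices) and 82.4% at 45:135. For d = 0.42 it gives 82.1% at 95:95 and 81.5% at 62:187. Over all eight stated splits the range is 80.8–82.5%. The figures are right under independence, with roughly 1 to 3 points of slack.

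**Step 2: allow for clustering in the intervention arm only.** In SD units:

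- DE = 1 + (m − 1) × ICC
- SE(true) = √(DE/n1 + 1/n2); SE(naive) = √(1/n1 + 1/n2)
- Power = Φ(d/SE(true) − 1.96)
- Type I error if clustering is ignored = 2[1 − Φ(1.96 × SE(naive)/SE(true))]

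Example at 45:135, m = 8, ICC 0.05:

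- DE = 1 + 7 × 0.05 = 1.35.
- SE(naive) = √(1/45 + 1/135) = 0.172.
- SE(true) = √(1.35/45 + 1/135) = 0.193, a ratio of 1.124.
- Power = Φ(0.50/0.193 − 1.96) = 73%.
- Type I error = 2[1 − Φ(1.96/1.124)] = 8.1%.

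| m, ICC | MORS-SF 65:65 | MORS-SF 45:135 | PHQ-8/GAD-7 62:187 | MORS-SF 62:187 | Type I error at 45:135, clustering ignored |
|---|---|---|---|---|---|
| 4, 0.01 | 80.8% | 81.9% | 80.9% | 92.1% | 5.3% |
| 6, 0.02 | 79.4% | 80.0% | 78.9% | 90.8% | 5.9% |
| 6, 0.05 | 76.7% | 76.0% | 74.8% | 87.9% | 7.2% |
| 8, 0.05 | 74.8% | 73.4% | 72.3% | 85.9% | 8.1% |
| 10, 0.10 | 65.8% | 61.2% | 60.0% | 75.0% | 13.0% |

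Under the same normal approximation the independence values are 81.3%, 82.8%, 81.8% and 92.7% for the four power columns. The type I error at 62:187 is the same to within rounding, because it depends on the allocation ratio and DE, not on total n.

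**Step 3: few groups.** At 8 per group, 45 women make about 6 groups (45/8 = 5.6). At 4 per group, 62 women make about 15 (62/4 = 15.5). A stricter Satterthwaite t, with about n1/m − 1 degrees of freedom for the clustered arm, gives 79%, 74% and 59% at 65:65 for (4, 0.01), (6, 0.05) and (10, 0.10). At 45:135 with m = 8 and ICC 0.05 it gives 61%, against 73% by the normal approximation.

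**The case against.** A reader might infer that the 80% power is not delivered and that the standard errors are wrong. The article does not support that without conditions. It gives neither ICC nor group size. At ICC 0.01, power at 45:135 stays at 80–82% for every m from 4 to 10, and at ICC 0.02 with small groups it stays at about 80%.

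Five further points limit the concern, and each stands at least in part:

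- **Analysed group size may be small.** The offer is open to any eligible pregnant person in the area, but only BiBBS participants enrolled from May 2022 are studied, and about 40% of enrolled women do not complete. At m = 4 and ICC 0.05, power at 45:135 is 79% and type I error 6.3%.
- **The primary outcome is protected at the recommended size.** At 62:187, MORS-SF power is about 86–88% at ICC 0.05 with 6 to 8 per group. This needs about 187 matched controls, and the article also presents 45 intervention women as a sufficient minimum.
- **Shared facilitators are not established.** The article names facilitator roles, not fixed people, and the deliverer is recorded session by session.
- **Exposure to the group varies.** Intention-to-treat includes everyone enrolled after the first home visit, so some may attend no group. It may also retain more women than the completer numbers used for sizing. Completers need six sessions; if all three one-to-one contacts count, that could mean only three group sessions.
- **The variance estimator could still be set in the statistical analysis plan,** which the article announces and which is not shown. The type I error figures therefore apply only if clustering is left out there too.

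The last point does not reach the sample size. The totals and the advice to enrol 99 are final statements in this article. A later variance correction would protect type I error but would also bring out any power shortfall. Nor does spare sample size cure the type I error: it is 8.1% at both 45:135 and 62:187 for m = 8 and ICC 0.05.

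**Conclusion.** The point holds in conditional form. Delivery is grouped in one arm, and neither the sizing nor the stated model allows for it. The stated 80% is correct under independence and has too little slack to absorb a moderate ICC.

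Over the assumed range (4 to 10 analysed women per group, ICC 0.01 to 0.10), by the normal approximation:

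- MORS-SF at 45:135: power 61–82%.
- PHQ-8 and GAD-7 at 62:187: power 60–81%.
- MORS-SF at 62:187: power 75–92%.
- Type I error at these 1:3 splits if clustering is ignored: 5.3–13%.

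The low end needs both large groups and a high ICC. At ICC 0.01 the effect is negligible. At the recommended recruitment, with the controls obtained, the power loss falls mainly on PHQ-8 and GAD-7. It would be wrong to conclude that the primary outcome is underpowered at that size in general.

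**What to change.** 1. Carry the course-group identifier into the analysis file. The service already records attendance and group-level delivery.
2. State in the analysis plan that the models allow for course group in the intervention arm, with controls as singletons: either a random effect for course group in that arm, or cluster-robust variance. Either way, apply a small-sample degrees-of-freedom correction, because there may be only about 6 to 15 groups.
3. Restate the power for the MORS-SF and for PHQ-8 and GAD-7 as conditional on an expected number of analysed women per group and on an ICC range, for example 0.01 to 0.10.

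This needs no change to the design or to data collection from participants. It costs somewhat wider intervals, less stable variance estimates when groups are few, and a less favourable stated power.
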